### Community awareness campaign

A community awareness campaign was prospectively planned to accompany both baseline and intervention phases of the HTN Program. The purpose of the community awareness campaigns was to address misconceptions about hypertension, increase awareness at the community level, and to generate uptake of treatment of hypertension at the primary healthcare level. The campaign is led by members of the study team and implemented by health educators who are part of the primary healthcare workforce and local residents of the communities in which the campaigns are held. Within each area council, campaigns are held and reviewed quarterly.

### Outcomes

#### Primary outcomes

The study’s co-primary implementation outcomes include reach, effectiveness, adoption, implementation, maintenance, acceptability, and cost of the multi-level hypertension control program. The study's co-primary effectiveness outcomes are the change in slope from baseline slope of monthly hypertension treatment rates (defined as using any blood pressure-lowering drug) and monthly hypertension control rates (defined as systolic blood pressure <140 mmHg and diastolic blood pressure <90 mm Hg) among participating primary healthcare centers. We chose this definition of control based on the 2019 Nigeria Hypertension Protocol.

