**Fig. 1 Fig1:**
[figure not shown]
Alignment of the KPNC and WHO HEARTS technical packages with the Hypertension Treatment in Nigeria Program Implementation Package. The HTN Program implementation package is developed from the Kaiser Permanente Northern California and WHO HEARTS technical packages. Each component of the HTN Program implementation package is developed and deployed at different levels of the health system in the Federal Capital Territory, Nigeria. These levels include the patient, health worker, health clinic, health system, and national policy. All images are from Flaticon.com

Hypertension is the most common cardiovascular disease (CVD) in Nigeria, found in 86.4% of CVD patients, and is prevalent in an estimated 29–38% adult Nigerians [8, 9]. Multiple efforts are underway to address the burden of hypertension in Nigeria by increasing awareness, treatment, and control rates. For example, the National Hypertension Control Initiative (NHCI) is being piloted in 12 facilities in Ogun and Kano states to increase hypertension awareness, diagnosis, treatment, and control [10, 11]. The Hypertension Treatment in Nigeria (HTN) Program described in this report represents separate, yet related work. Both programs aim to lower hypertension-related morbidity and mortality, as well as strengthen hypertension diagnosis and management at the primary healthcare level through team-based care. More robust primary healthcare services will alleviate time and resource burdens on both patients and healthcare providers at secondary and tertiary care centers where hypertensive services have historically been provided in Nigeria.

Our aim was to implement and evaluate a large-scale hypertension treatment and control program within 60 public primary healthcare centers in the Federal Capital Territory, Nigeria through a type 2 hybrid effectiveness-implementation, interrupted time series design with outcomes measured using the RE-AIM framework [12].

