### Participants

Prior to study initiation, we identified and assessed all public primary healthcare centers within the Federal Capital Territory of Nigeria (*N*=243) based on staffing, patient volumes, and functionality. To be eligible, primary healthcare centers had to have at least two full-time staff, be accessible to the study team by road and in all seasons, and be functional (i.e., defined as open at least between the hours of 8 AM and 4 PM and providing the minimum service package for primary healthcare centers). Sites were randomly selected through a multi-stage sampling frame including stratification by caseload and geography. Selected primary healthcare centers were invited to participate in the program, and all 60 (100%) of invited sites agreed to participate. Each selected primary healthcare center participated in a hypertension-adapted Service Availability and Readiness Assessment (SARA) based on the WHO instrument prior to initiation of the control phase to evaluate and confirm capacity and readiness for the study [19].

During the control and intervention phases, all adults (≥ 18 years) who presented at a participating site with persistently elevated blood pressure (systolic blood pressure ≥ 140 mmHg or diastolic blood pressure ≥90 mmHg, measured twice) or a history of hypertension were eligible for inclusion. Patients were registered in the study database through entry in a site-based patient registry log and empaneled in the hypertension cohort (Additional file 3). Informed consent was not collected per the Common Rule [20].

We collected data on paper case report forms, which were designed to be included in the patients’ medical files at each primary healthcare center (Additional file 4). Paper case report forms are completed and maintained by the CHEW at registration and each subsequent patient visit. After the patient visit, a record information officer at the site abstracted information from the patient case report form into the electronic REDCap database [21]. The REDCap database was hosted at the University of Abuja, and each participating primary healthcare center was provided with a tablet upon which the REDCap mobile application was installed. Data capture included, but was not limited to socio-demographics, medical history, anthropometrics, blood pressure values, relevant laboratory studies when available (e.g., serum potassium, serum creatinine), medications, side effects, adverse events, counseling, and patient vital status.

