Intervene with patients/consumers to enhance uptake & adherence	Health system	Community awareness campaigns are conducted in each area council to increase awareness of and demand for hypertension services.	• Hypertension patient registry and empanelment • Community awareness and mobilization campaigns • Health coaching and home BP monitoring
*Utilize financial strategies*			
Alter incentive/allowance structures	Health worker	Frontline healthcare staff are compensated for registration of patients through monthly stipends of at least 10,000 naira each.	• Team-based care and community health extension worker provided hypertension management
Alter patient/consumer fees	Health system	Free or low-cost medicines are made available to hypertensive patients registered in the Program.	• Simplified treatment guideline • Fixed-dose combination • Access to essential medicines and technology
*Change infrastructure*			
Change physical structure and equipment	Health facility	All sites were equipped with functional automated blood pressure monitors, paper case report forms, electronic tablet, and data connections.	• Hypertension patient registry and empanelment
Change record system	Program	Create an electronic-based data capture system to supplement the paper-based system for rapid data collection and quality assurance.	• Performance and quality reporting
Change service sites	Program	Patients who would typically seek care in a tertiary care center are able to find the same hypertension care in their local health clinic. Home-based blood pressure monitoring and health coaching for individuals with persistently elevated blood pressure and social disadvantage	• Team-based care and community health extension worker provided hypertension management • Health coaching and home BP monitoring
Drug Revolving Fund	Health System	Addition of hypertension medications to the existing drug revolving fund.	• Simplified treatment guideline • Fixed-dose combination • Access to essential medicines and technology

*Abbreviations*: *BP* Blood pressure, *CHEW* Community health extension worker, *CHO* Community health officer, *HTN* Hypertension Treatment in Nigeria, *PHC* Primary healthcare center, *WHO* World Health Organization

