**Fig 3 Fig3:**
[figure not shown]
CONSORT Flowchart of Enrollment, Eligibility, and Analytic Sample Size in the Hypertension Treatment in Nigeria Program from January 1, 2020, through May 5, 2022

The statistical analysis will be performed using the intention to treat principle (i.e., all patient visits recorded in the database will be included and considered exposed to the intervention or unexposed according to the overall program timeline, regardless of when the intervention was actually implemented). The statistical design of the program intervention includes evaluation of effectiveness and implementation co-primary outcomes, which is consistent with the type 2 hybrid design. For implementation outcomes, we will use quantitative and qualitative analysis using the RE-AIM framework to triangulate routinely collected data to evaluate the reach, secondary effectiveness, adoption, implementation, maintenance, acceptability, and cost of the implementation package [12]. We will seek to explore and explain variability across key subgroups, including age, sex, and geography.

For effectiveness outcomes, we will use an interrupted time series evaluation with aggregate measures of system-level monthly treatment and control rates to evaluate temporal trends. We will evaluate change in temporal trends for primary and secondary outcomes through segmented linear regression by aggregating data across primary healthcare centers by month. To evaluate effects of each implementation package component and time variance in implementation on our primary outcomes, we will use patient-level mixed-effects models including random effects to account for clustering at the primary healthcare center level. We will perform sensitivity analyses by both excluding and restricting repeated measures of the same patients over the program period.

For the home blood pressure and health coaching sub-study, we will use analysis of covariance, controlling for baseline clinic-measured systolic blood pressure and medication to estimate the effect of a community health extension worker-led health coaching and home blood pressure monitoring on a 12-week change in systolic blood pressure compared with propensity-matched patients in the participating sites as controls. For implementation outcomes, we will adapt the RE-AIM framework and use quantitative data to evaluate the reach, effectiveness, adoption, implementation, maintenance, and cost of the interventions.

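### A shift after December 2020 in the share of patients already on drugs at registration would be mixed into the co-primary slope changes, mainly for treatment, and no planned analysis separates it

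*Protocol article*

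**What the plan says.** Under Primary outcomes, the "co-primary effectiveness outcomes are the change in slope from baseline slope" of two monthly rates. The first is "monthly hypertension treatment rates (defined as using any blood pressure-lowering drug"); the second is control below 140/90 mmHg. Treatment need not be new or started at the center.

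Under Participants, adults with persistently raised blood pressure "or a history of hypertension were eligible for inclusion", in both phases. Under Statistical analyses, "all patient visits recorded in the database will be included and considered exposed to the intervention or unexposed according to the overall program timeline", and the model is "segmented linear regression by aggregating data across primary healthcare centers by month".

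The Background describes existing care "at secondary and tertiary care centers where hypertensive services have historically been provided in Nigeria". Table 2 lists a change of service site: "Patients who would typically seek care in a tertiary care center are able to find the same hypertension care in their local health clinic". It also lists a change in fees: "Free or low-cost medicines are made available to hypertensive patients registered in the Program". Table 2 ties the fee strategy to the treatment guideline, fixed-dose combination and essential medicines components, and the service-site strategy to team-based care and home monitoring. Table 1 starts all of these in December 2020, except home monitoring (September 2022, 10 sites). The Intervention section states that only the registry component ran during the control phase.

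**The concern.** A patient who already takes a drug from a hospital and then registers at a center enters the treatment numerator at the first visit, although the program did not start that treatment. A stable share of such patients does no harm, because the baseline level and slope absorb it. A share that changes when the package starts is different: the control-phase trend cannot predict it, so the model assigns it to the intervention.

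The reasons to move arise at the interruption, which makes such a change plausible. Moving care closer to home is a real benefit, but it belongs under reach. The Discussion rests the case for wider use on the co-primary effectiveness outcomes, so a reader needs to know how much of a slope change comes from who attends.

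**Working it through.** **Inputs from the protocol (Sample size):** baseline treatment 20% and control 10%; underlying trends 0.10 and 0.05 points per month; intervention slopes 0.57 and 0.44; end rates 42.5% and 27.0% at 48 months; 9 + 39 months. **From Timeline:** the actual phases are 11 + 37 months. **Assumed:** the share of transfers already on drugs, how it grows, and the fraction of them controlled.

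**1. The plan's own figures.** With 47 monthly steps from month 1 to month 48:
- Treatment: 20 + 0.10×9 + 0.57×38 = 42.56, against 42.5 stated.
- Control: 10 + 0.05×9 + 0.44×38 = 27.17, against 27.0 stated.

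Solving back for the slopes gives 0.568 and 0.436, which round to the stated values. Reading 0.57 as the added slope would give 20 + 0.10×47 + 0.57×38 = 46.36, which does not fit. The planned slope changes are therefore 0.57 − 0.10 = 0.47 and 0.44 − 0.05 = 0.39 points per month.

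**2. Mixture model.** Let s(t) be the share of visits by transfers already on drugs, zero through month 11, and let nothing else change:

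y(t) = (1 − s(t))·(20 + 0.10t) + s(t)·100

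At month 48 the other attenders are at 24.8%. If transfers then make up 10% of visits, y = 0.90×24.8 + 10 = 32.3%. At 25%, y = 0.75×24.8 + 25 = 43.6%.

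**3. Segmented fit to y(t)**, interruption after month 11, least squares. The table gives the false treatment slope change in points per month for transfers reaching 10% (25%) of visits:

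| Growth of s(t) | Level term in model | No level term |
|---|---|---|
| Linear to month 48 | +0.20 (+0.51) | +0.20 (+0.49) |
| Ramp over 12 months, then flat | +0.14 (+0.35) | −0.23 (−0.57) |
| Ramp over 6 months, then flat | +0.07 (+0.17) | −0.49 (−1.23) |
| Ramp over 12 months, then falling to half | +0.02 (+0.06) | −0.43 (−1.07) |
| Step at month 12 | −0.01 (−0.03) | −0.76 (−1.90) |

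With a level term the step goes into the level: at month 12 it is 0.10×(100 − 21.2) = 7.9 points for the 10% case.

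**4. Control.** Replace the base by 10 + 0.05t and assume that half of transfers are controlled. Linear growth gives +0.10 (+0.25), against 0.39 planned. The 25% case ends at 0.75×12.4 + 0.25×50 = 21.8%, against 27.0%.

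**5. Share needed to reproduce the planned end rates by transfer alone.**
- Treatment: (42.5 − 24.7)/(100 − 24.7) = 23.6% of month-48 visits if the other attenders follow the trend, or (42.5 − 20)/(100 − 20) = 28.1% if they stay at 20%.
- Control: about 39–43% of visits if half of transfers are controlled; about 22–24% if 80% are.

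**6. Planned analyses that come closest.** None is defined by drug use on arrival:
- sensitivity analyses on repeated measures, and patient-level mixed models (Statistical analyses);
- exploratory subgroups by duration of registration and treatment regimen (Subgroup analyses);
- sensitivity analyses using contextual factors (Context tracker);
- the sociodemographic comparison with the catchment area (Table 3).

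The limitations in the Discussion cover linearity and imprecision, not a change in who attends.

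**The case against.** The strongest objection is that the outcome is a slope, and a slope is biased upward only by an inflow that keeps growing. The pull of cheap medicines may be front-loaded: Table 1 describes initial supplies that primed a Drug Revolving Fund, and the Interim analyses section reports worry that leaving free drugs could reduce enrollment and retention. An early or fading inflow gives little slope bias with a level term, and bias against the program without one. This stands, and it is why no single figure or direction can be given.

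Three further points also stand. Already-treated patients could register in the control phase, and the awareness campaign ran in both phases, so only a change in share matters. The 20% base is a literature estimate for the Territory; at an assumed 50% base the linear 10% case falls to +0.12. And Table 2 says only that tertiary-care patients can find care locally. A reader might infer that the package draws in patients who are already treated and often controlled, but the protocol reports neither how many transfer nor their drug use or control.

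It can also be said that a split by entry treatment belongs in the analysis plan, which is not shown. That limits the point to a request for a prespecified sensitivity analysis. It does not remove it, because the protocol itself fixes the outcome definition, the analysis set and the aggregation that create the exposure.

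**Conclusion.** The point holds as a risk of unknown size that no planned analysis measures. Under the assumptions above and with a level term, the false treatment slope change runs from about zero (step) to +0.20 for transfers reaching 10% of visits and +0.51 for 25% (linear growth), against about 0.47 planned. Without a level term, every assumed shape except steady linear growth biases the slope downward. Control is less exposed and depends on how many transfers are controlled.

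A reader might go further and infer that the treatment rate will reach its planned value with nobody newly treated. The arithmetic permits this only if about 24–28% of month-48 visits are such transfers, and the plan's slope only if the inflow grows steadily throughout. The protocol supports neither. In the 25% case with half of transfers controlled, the planned control rate is not reached either.

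**What to change.** Keep the crude series as the primary analysis and add the following before analysis:

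1. Classify each patient by drug use before the registration visit, from the medical history and medication data listed under Participants.
2. Report the already-treated share among new registrants, by month, across both phases. A flat share largely answers the concern.
3. Prespecify a sensitivity segmented regression for both co-primary outcomes, with a level term and with the already-treated/not-treated mix standardised to its control-phase share.
4. State that the effectiveness conclusion will be qualified if the standardised slope change is materially smaller than the crude one, and say beforehand what counts as materially smaller.

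The cost is analysis text and programming, provided that the case report form distinguishes drugs taken on arrival from drugs prescribed at that visit. The article does not show this, so it must be checked first. Standardising removes only the change in entry mix. A series restricted to patients untreated at registration may be shown descriptively but should not carry the claim: it starts near zero and rises mechanically as follow-up visits accumulate.

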#### Secondary effectiveness

The study’s secondary effectiveness outcomes include (1) mean systolic blood pressure and diastolic blood pressure among eligible clinic patients with hypertension, and (2) rates of single versus two- or three-drug blood pressure-lowering medication use (including use of fixed-dose combination therapies).

#### Safety

The study’s safety outcomes include (1) proportion of participants with any potentially relevant side effect, including provider diagnosis of angioedema, acute kidney injury (defined as relative increase in serum creatinine by 50% or an absolute increase by 0.3 mg/dl [>0.26 μmol/L]), electrolyte abnormalities (defined as serum potassium < 3.5 or >5.5 mEq/L or serum sodium <125 or > 145 mEq/L), syncope, or dizziness, (2) rate of relevant side effects at the participant level (i.e., count per participant), and (3) proportion of participants with any serious adverse event according to Good Clinical Practice definition.

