#### Missing data

Missing data are identified through bi-weekly data quality reports and resolved with the responsible site where feasible. Complete case analyses will be performed in the primary analysis, and multiple imputation will be used for sensitivity analyses to explore the robustness of results.

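### Safety outcome (1) pools laboratory-defined and symptom events in one proportion of participants, although laboratory values are recorded only where they exist, so it cannot be read without the number tested

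*Protocol article*

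**What the plan says.** Under Outcomes, Safety, the first outcome is the "proportion of participants with any potentially relevant side effect, including provider diagnosis of angioedema, acute kidney injury", with electrolyte abnormality, syncope and dizziness completing a list of five components. Two of the five are given laboratory definitions. Acute kidney injury is "defined as relative increase in serum creatinine by 50% or an absolute increase by 0.3 mg/dl", and electrolyte abnormality is "defined as serum potassium < 3.5 or >5.5 mEq/L or serum sodium <125 or > 145 mEq/L". The second safety outcome counts the same kind of events per participant. The third is any serious adverse event.

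The Participants section lists among the data captured "relevant laboratory studies when available (e.g., serum potassium, serum creatinine), medications, side effects, adverse events". The article gives no schedule for laboratory tests.

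Two general rules could bear on participants without results. Statistical analyses says that "all patient visits recorded in the database will be included and considered exposed to the intervention or unexposed", according to the program timeline. Missing data says: "Complete case analyses will be performed in the primary analysis, and multiple imputation will be used for sensitivity analyses". Neither rule is linked to the safety outcomes, and the Safety section gives no separate denominator for the laboratory components.

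**The concern.** An increase in creatinine can be seen only if there are at least two values. An electrolyte abnormality can be seen only if there is at least one potassium or sodium value. Syncope and dizziness can be asked about at any visit, and angioedema rests on a provider's diagnosis. One proportion over all five therefore mixes events that can be ascertained in everyone with events that can be ascertained only in those who were tested.

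At stake is the description of kidney and electrolyte harm in a program that extends drug treatment and had registered more than 16,000 people by May 2022. A low proportion could mean few events or few tests, and the outcome as defined does not let a reader tell which. The per-participant count in outcome (2) has the same weakness.

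**Working it through.** The article states no safety event rate and no testing coverage, so there is no figure of its own to reproduce. All rates below are assumptions that show the mechanism and its range.

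**Inputs (assumed).** p = 3%, true risk of a laboratory-defined event. q = 5% or 2%, risk of an event that needs no test, independent of p. t = 5%, 10% or 30%, share of participants with adequate tests.

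**Reading A: untested participants are non-events, and testing is unrelated to risk.**

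Laboratory component shown = p × t. Composite shown = 1 − (1 − q)(1 − p × t). True composite = 1 − (1 − q)(1 − p).

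True composite: for q = 5%, 1 − 0.95 × 0.97 = 7.85%; for q = 2%, 1 − 0.98 × 0.97 = 4.94%.

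| Coverage t | Laboratory component (true 3%) | Composite, q = 5% (true 7.85%) | Composite, q = 2% (true 4.94%) |
|---|---|---|---|
| 5% | 0.15% | 5.14% (1.5-fold low) | 2.15% (2.3-fold low) |
| 10% | 0.30% | 5.29% (1.5-fold low) | 2.29% (2.2-fold low) |
| 30% | 0.90% | 5.86% (1.3-fold low) | 2.88% (1.7-fold low) |

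Example at t = 10%, q = 5%: 1 − 0.95 × (1 − 0.03 × 0.10) = 1 − 0.95 × 0.997 = 0.05285.

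The laboratory component is understated 20-, 10- and about 3-fold. The composite is understated far less, because the events that need no test are still counted.

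**Reading B: the complete-case rule is applied to the composite.**

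Participants without adequate tests are dropped, including those with observed symptoms. For illustration, take 16,000 participants: 16,000 × 5% = 800 would have an event needing no test. At t = 10%, with testing unrelated to those events, 800 × 90% = 720 of them would be discarded.

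Those who remain may not be typical. If tested patients have R times the laboratory risk of untested patients, the risk among the tested is R × p / (tR + 1 − t). With R = 2 (assumed), t = 10% and p = 3%, this is 0.06 / 1.10 = 5.45%, against a true 3%. The composite among the tested becomes 1 − 0.95 × (1 − 0.0545) = 10.2%, against a true 7.85%.

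**The two denominators together.** In the same targeted-testing case, detected laboratory events over all participants are 0.10 × 5.45% = 0.55%. The true 3% lies between 0.55% (all participants) and 5.45% (tested only). Neither figure alone estimates it. The all-participant figure cannot exceed the truth. The tested-only figure is too high when testing favors patients at higher risk.

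**The case against.** The strongest reply is that the article does not say what a critical reader might infer. It speaks of participants, not of all participants, and nowhere states that an untested person is scored as event-free. Its only general missing-data default, complete cases, points the other way, and with targeted testing it could overstate risk. The denominator for individual components is also something a condensed article may leave to an analysis plan or case report form that is not shown here. Safety does not rest on this outcome alone, since serious adverse events need no laboratory result.

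Much of this stands. Scoring untested participants as negatives is the plain reading of a yes/no measure per participant, not a stated rule. It is tempting to conclude that the safety result is understated 3- to 20-fold, or that a doubling of coverage between phases would double it. Those ratios belong to an isolated laboratory component with testing unrelated to risk. For the composite with q = 5%, a rise in coverage from 5% to 10% moves the figure only from 5.14% to 5.29%. The article also plans no comparison of safety between phases: its trend analysis is for primary and secondary outcomes, and safety has its own heading.

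The reply does not remove the problem. The article itself fixes the list of components, pools them in one proportion, and makes two of them depend on tests that may not have been done. One reading dilutes the laboratory events and the other discards observed symptoms. A denominator chosen later in an analysis plan would not repair the composite, because its components need different denominators.

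**Conclusion.** The point holds as a defect in how safety outcome (1) is built, and outcome (2) inherits it. Events that depend on a test and events that do not are pooled in one proportion while testing is opportunistic, so the result cannot be interpreted without the number tested.

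The size depends on coverage and event rates that the article does not give. On the plain reading with p = 3% and 10% coverage unrelated to risk, the laboratory component shows 0.3%. The composite shows 5.29% against 7.85% with q = 5%. Over the assumed ranges, the composite is understated about 1.3- to 2.3-fold.

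The documents do not support a flat statement that harm is understated. That is conditional on the plain reading, it does not concern events that need no test, and under complete-case handling with targeted testing the error can run the other way. Nor do they support a claim about bias between phases: no such safety comparison is stated, and if one were made, its direction would depend on how testing changed.

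**What to change.** Split safety outcome (1):

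- Report angioedema, syncope and dizziness as a proportion of all participants.
- Report acute kidney injury and electrolyte abnormality separately, each over two denominators: all participants, labeled as detected events, and participants with adequate tests (at least two creatinine values, or at least one potassium or sodium value).
- Beside these, give the number and percentage tested in the control and intervention phases.
- State that untested participants are not known to be event-free.
- Apply the same split to the count per participant in outcome (2).

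The cost is revised outcome wording and a few lines of analysis code on data already captured in REDCap. No added blood tests are needed. The drawback is that the tested-only figure comes from a smaller, selected group and may overstate risk. A tested-only denominator is therefore not a remedy by itself, and both denominators should appear with the coverage.

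### The absolute creatinine criterion for acute kidney injury is printed with an SI value about 100 times too small (0.3 mg/dl is about 26.5 μmol/L, not 0.26)

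*Protocol article*

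**What the plan says.** The Safety subsection of Outcomes in the protocol article lists three safety outcomes. The first is the "proportion of participants with any potentially relevant side effect, including provider diagnosis of angioedema, acute kidney injury", followed by electrolyte abnormalities, syncope and dizziness. Acute kidney injury has two alternative criteria, of which either is enough: a "relative increase in serum creatinine by 50% or an absolute increase". The absolute criterion is printed in two units, as "an absolute increase by 0.3 mg/dl [>0.26" μmol/L, with the second figure in square brackets as the SI form of the first.

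The Participants subsection says that the data captured include "relevant laboratory studies when available (e.g., serum potassium, serum creatinine"). It names no reporting unit for creatinine. The article does not restate or correct the threshold anywhere else.

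**The concern.** A bracketed figure after a threshold should be the same threshold in other units. Here the two figures cannot both be right, and the gap is far larger than rounding could explain.

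The stake is how one safety event is classified. Because the relative and absolute criteria are joined by 'or', the looser one governs. An absolute criterion of 0.26 μmol/L lies within ordinary measurement noise, so anyone who applied it to values in μmol/L would classify almost every upward difference between two creatinine results as kidney injury. Someone who applied 0.3 mg/dl to the same patients would not. The event feeds the first safety outcome and, as a side effect, could also enter the second, the "rate of relevant side effects at the participant level (i.e., count per participant").

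**Working it through.** **Inputs**
- From the article (Outcomes, Safety): absolute criterion 0.3 mg/dl; bracketed SI value 0.26 μmol/L; relative criterion 50%; criteria joined by 'or'.
- Not in the article: molar mass of creatinine, about 113.12 g/mol. This is a physical constant; 113.0 to 113.2 was tried as a range.

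**Step 1. Try to reproduce the printed figure**
- Conversion: μmol/L = mg/dl × 10,000 / molar mass.
- Factor: 10,000 / 113.12 = 88.4.
- 0.3 × 88.4 = 26.5 μmol/L (26.50 to 26.55 over the molar-mass range).
- The printed value is 0.26, so it is not reproduced.

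**Step 2. Size of the disagreement**
- In reverse: 0.26 / 88.4 = 0.0029 mg/dl, against 0.3 mg/dl.
- Ratio: 26.5 / 0.26 = 102.

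**Step 3. Could another reading rescue the figure?**
- Unit meant as mmol/L: 0.3 mg/dl = 0.0265 mmol/L, not 0.26.
- 0.26 meant as mg/dl: 0.26 × 88.4 = 23.0 μmol/L, which does not match 0.3 mg/dl either.
- Decimal point two places out: 26 μmol/L = 26 / 88.4 = 0.294 mg/dl, which rounds to 0.3. This is the only reading tried that fits the printed digits.

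**Step 4. What the bracketed figure would do if applied to values in μmol/L**

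*Effect on the 50% criterion.* A 50% rise is smaller than the absolute criterion only when the baseline is below twice that criterion.
- With 0.26 μmol/L: 2 × 0.26 = 0.52 μmol/L. At any baseline above this, a patient who meets the 50% criterion has already met the absolute one, so the 50% criterion adds nothing.
- With 26.5 μmol/L: 2 × 26.5 = 53 μmol/L. Below this baseline the 50% criterion still does work of its own.

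*Effect of measurement noise (illustration; baseline and CV are assumptions).* Take a baseline of 80 μmol/L, no true change, and a total measurement CV of 2%, 4% or 6%.
- 0.26 is 0.33% of 80; 26.5 is 33% of 80.
- SD of the difference between two results = 80 × CV × √2.
- Share of apparent rises above a threshold t = 2 × [1 − Φ(t / SD)].

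| CV | SD of difference (μmol/L) | Share of rises > 0.26 | Share of rises > 26.5 |
|---|---|---|---|
| 2% | 2.26 | 91% | about 0 |
| 4% | 4.53 | 95% | about 0 |
| 6% | 6.79 | 97% | about 0.01% |

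If results are recorded as whole μmol/L, every rise is at least 1 and therefore exceeds 0.26.

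**The case against.** The strongest defence accepts the slip and disputes its consequence. The mg/dl value comes first and the SI value is a gloss on it. Nothing in the article shows that any center reports in μmol/L, or that 0.26 is programmed in the database or analysis code; the case report form is an additional file that is not shown. The wording may also mean that events rest on a provider's diagnosis rather than on a computed threshold. And 0.26 μmol/L is so implausible that a user would probably notice it. All of this stands. It limits the point to a wrong printed figure whose effect on results is unknown and may be nil.

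Three stronger readings are tempting, and the article does not support them.
- *A reader might infer that the safety results will be inflated.* That needs the SI figure to be applied to values in μmol/L, which the article does not state.
- *A reader might infer, because laboratory values are collected only when available, that untested participants will count as event-free and that the kidney injury proportion is understated by some multiple.* The article sets no such rule. Its Missing data subsection speaks of complete case analysis with multiple imputation as sensitivity; it does not address safety specifically, but it lends no support to imputing 'no event'. The article gives no testing rate from which to derive a multiple. Kidney injury is also only one component of a composite that includes syncope and dizziness, which need no laboratory test. Denominators of this kind are commonly left to the analysis plan.
- *A reader might infer that the side-effect rate is wrongly defined because it is not scaled to follow-up time.* The article labels it openly as a count per participant. Scaling by person-time is again a matter commonly left to the analysis plan.

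**Conclusion.** The point holds as an error in a printed outcome definition. The two forms of one threshold differ about 102-fold, and the SI figure cannot be reproduced from the mg/dl figure under any reading tried. The conversion rests only on the molar mass of creatinine, and the result barely moves over the range tried.

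The effect on results is conditional. If 0.26 μmol/L were applied to values in μmol/L, nearly any rise would qualify: 91% to 97% of pure-noise rises under the assumed baseline of 80 μmol/L and CV of 2% to 6%. If only mg/dl is used, nothing changes. The article does not settle which case applies.

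The severity is minor. One component of a safety outcome is affected; the co-primary treatment and control outcomes, the segmented regression and the sample size are not.

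**What to change.** Reconcile the bracketed SI value with the mg/dl value in the Safety subsection; 0.3 mg/dl of creatinine converts to about 26.5 μmol/L. Then confirm three things: the unit in which creatinine is recorded at the centers, the threshold (if any) shown on the case report form, and the threshold and unit in the analysis code. If any kidney injury events have already been derived with 0.26 μmol/L, derive them again.

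The cost is one corrected figure and a short check of the form and code. No new data are needed.
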